### BRIEF questionnaire

The Behavior Rating Inventory of Executive Function (BRIEF) is an assessment of behaviors at home for children and adolescents aged 5–18 years [67]. One parent or guardian for each child was asked to answer the questionnaire. After 3–4 weeks, parents were reminded to return the questionnaire via a message on the school’s intranet. Parents rated their child’s behavior on a three-point Likert scale (never, sometimes, and often). Eight scales were obtained (Initiate, Working Memory, Plan/Organize, Organization of Materials, Monitor, Inhibit, Shift, Emotional Control), along with a metacognition index (MCI), a behavior regulation index (BRI), and a global executive composite (GEC). The BRIEF Parent Form was normed on 1419 control children and 852 children from referred clinical groups; the Cronbach coefficient measure of internal consistency ranged from 0.80 to 0.98 for the parent and teacher form in clinical and normative samples [67].

### Creativity

Creativity was assessed because of a potential executive involvement in creative thought. We used the 30-minute standardized Figural Torrance Tests of Creative Thinking (TTCT): Thinking Creatively with Pictures, which requires the subject to reflect upon their life experiences. It is the most widely used test of creativity [68] and the most referenced creativity test [69]. The child was given three different activities and asked to draw and title one drawing to each task (pictures). Due to the mean child age of 7.2 ± 0.3 years, the Figural TTCT was chosen over the Verbal TTCT in liaison with the developer (Scholastic Testing Service) to avoid test results being influenced by writing skills. The Figural TTCT assesses the following mental characteristics: i) Fluency, a measure of the total number of interpretable, meaningful, and relevant ideas generated in response to the stimulus ii) Flexibility, related to the number of different categories of relevant responses iii) Originality, a measure of the statistical rarity of the responses, iv) Elaboration, related to the number of added ideas. The test was conducted according to the developer’s manual. It was completed individually with paper and pencil in a classroom, but was administered as a group test. After a general presentation of the test, the children were presented to each of the three tasks separately. Ten minutes were given to complete each activity.

In Activity I, the child constructed a picture using a pear or jellybean shape provided on the page as a stimulus. The stimulus was required to be an integral part of the picture construction. Activity II required the child to use 10 incomplete figures to make an object or picture. Activity III, was composed of three pages of lines or circles which the child should use as a part of the picture [70]. No aids were permitted.

### Aerobic fitness

Aerobic fitness was assessed using the Andersen test, an intermittent shuttle run test [71] that has previously been shown to be easy applicable and valid (*r* = 0.68) for measuring aerobic fitness in younger study populations. The children were instructed to run as far as possible in 10 min back and forth between two lines 20 m apart. This was performed in bouts of 15 s running followed by 15 s rest before the next bout. Participants were carefully instructed to take no more than two steps to stop after each bout of running and to sit down after the last bout facing the running direction to allow measurement of the distance of the last incomplete 2x20m round. Test personnel controlled the time and used a whistle to start and stop the participants. The test result was total distance in meters which has been validated against direct measures of maximal VO_2_-uptake [71, 72]. The Andersen test was found to be reproducible and valid (r2 = 0.53, *n* = 32, *p* < 0.001) for determining intermittent exercise capacity and estimating maximal oxygen uptake for children aged 6–9 years [72].

### Anthropometric measures

Body height was measured without shoes to the nearest 0.5 cm using a Harpenden stadiometer (West Sussex, UK). Body mass was measured in light clothing to the nearest 0.1 kg using an electronic scale (Tanita BWB-800, Tokyo, Japan). Body mass index was calculated as body mass (kg) divided by height (m) squared.

## Assessment of classroom physical activity and total physical activity

Intervention compliance was assessed using different methods targeting teachers and parents as well as the children. This included video analysis of lessons, SMS-tracking, and accelerometry.

### Video analysis

Math lessons were video-filmed for one week halfway during the intervention. The video camera (Mini DV DVR AVI Hidden Spy Video Camera & Voice recorder, AEE, China) was hidden to avoid behavioral change due to the camera attention. The teacher was asked to start and stop the camera at the beginning and end of the lesson.

### SMS-tracking

Short Message Service (SMS)-tracking was used to collect data from teachers about types and frequency of classroom PA elements. Each month, the math teachers received an SMS every day for one week asking about length, intensity of the PA (with specific examples of the three different intensities) and the teacher’s motivation for implementing PA in the math lessons. SMS-tracking was also used to assess the child’s leisure PA and school transport. This was accomplished by asking the parents to answer three questions. Parents received an SMS once a week during the entire intervention (see Appendix 3 for questions to teachers and parents).

### Classroom PA and total PA by students using accelerometry

The level of PA during math lessons and total daily PA were assessed using accelerometry (ActiGraph, GT3X and GT3X+, ActiGraph LLC, Pensacola, FL, USA). PA data were collected for eight days at baseline and again just before follow-up measurements. The accelerometers were randomly distributed by the research staff to all participants, who were instructed to wear the monitor during waking hours for at least eight consecutive days. Assessment periods were balanced between control and intervention schools. To eliminate reactivity bias, the monitors started recording the day after distribution. Epoch length was set to 2 s but subsequently downloaded in 10-s epochs. A sequence of more than 60 min of consecutive zeros was considered non-wear time and eliminated from the analysis. To account for children who failed to remove the monitor at night, only activity recorded between 6 am and 10 pm was analyzed. A valid measurement of total PA was defined as a minimum of four days with at least 10 h of recorded activity each day. For PA levels during math lessons only one valid day of measurement was required for inclusion in the analysis. Propero software (University of Southern Denmark, Odense, Denmark) was used to prepare the data for further analysis and to specify the time-points at which, according to the class schedule, math lessons took place. Total PA was expressed as mean counts per minute (cpm) and mean minutes in moderate-to-vigorous physical activity (MVPA) per day. Intensity cut-off points by Evenson et al. were used to define MVPA [73].

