## The classroom-based PA intervention

The active math intervention consisted of math teaching that implemented PA in the classroom as a facilitating instrument. The intervention period lasted one school year, during which the students received on average 6 math lessons of 45 min per week with physically active teaching. PA in this math intervention was defined as any bodily movement produced by skeletal muscles that resulted in increased energy expenditure [49]. This is similar to the definition known as movement integration (MI) [50].

Each 45-minute lesson consisted of at least 15 min of PA spread over the lesson. Math lessons usually took place in the classroom, but were also held in other school areas such as corridors and surrounding outdoor areas. Sedentary activities were limited to periods of maximum 20 min, given that most students are unable to sustain attention on one thing for more than about 20 min at a time [51]. The rationale behind the active math was that if an abstract phenomenon is connected to a concrete bodily experience other than just seeing or hearing it, the comprehension and memory of the given phenomenon could be optimized (e.g. [52, 53]). In addition, we expected that breaking up the cognitive load imposed by a learning task would limit overload of working memory in the children and thus help maintain focus [54]. Studies have detected limited working memory capacity in children, and spreading the load across different working memory subsystems might prevent overload in one specific subsystem [55–57]. The active math lessons followed the principles of “learning by doing” and the development of practical life skills that are crucial to children’s education [58]. This is related to experiential learning theory, i.e. learning through action and experience as opposed to through repetition [59, 60]. The active math approach was adopted for all math lessons for the entire school year. Appendix 1 provides examples from the active math intervention.

Children in the control schools received regular classroom instruction, also with an average of 6 math lessons of 45 min per week. The math teachers in the control schools were asked not to make any changes to their usual teaching methods before the study endpoint measurements. This was accepted with the agreement that at the end of the study, these teachers would receive the same training in physically active math teaching as the teachers in the intervention group.

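### The 60-minute non-wear rule cannot detect a monitor taken off for one 45-minute math lesson, so that lesson counts as zero activity (minor; compliance measure only)

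*Protocol article*

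**What the plan says.** All of the accelerometer rules stand in the protocol article under *Classroom PA and total PA by students using accelerometry*. The section covers two measures: "The level of PA during math lessons and total daily PA were assessed using accelerometry".

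- Non-wear, stated once and for both measures: "A sequence of more than 60 min of consecutive zeros was considered non-wear time and eliminated from the analysis".
- Validity of total activity: "A valid measurement of total PA was defined as a minimum of four days with at least 10 h of recorded activity each day".
- Inclusion for lesson activity: "For PA levels during math lessons only one valid day of measurement was required for inclusion in the analysis".
- Location of lessons: the processing software was used "to specify the time-points at which, according to the class schedule, math lessons took place", so a lesson is found from the timetable and not from evidence of wear.

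The lesson length comes from *The classroom-based PA intervention*: "Each 45-minute lesson consisted of at least 15 min of PA spread over the lesson". The same section gives the frequency: "the students received on average 6 math lessons of 45 min per week with physically active teaching", with the same average number and length of lessons in the control schools. The section states no shorter zero-run limit and no minimum wear time within a lesson.

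**The concern.** A non-wear threshold suited to a whole day is applied to a window shorter than the threshold. A gap that fills one lesson exactly is therefore indistinguishable from a lesson in which the child did not move, and the stated rules resolve the doubt in favour of no movement.

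Lesson activity is one of the measures of whether the intervention was delivered (*Assessment of classroom physical activity and total physical activity*). The *Discussion* also says that activity in specific periods, math lessons among them, can be analyzed by linking the data to the timetable. False zeros understate lesson activity in whichever arm they occur. They also add error to a child's value, which would carry into any association analysis that uses lesson activity as the exposure. The one-day inclusion criterion means that some children may have very few lessons over which to average such an error out.

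**Working it through.** The plan gives no figure to reproduce here, so the check is of the rule itself.

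**Inputs from the document:** non-wear is a zero run longer than 60 min; a lesson is 45 min; about 6 lessons per week; data in 10-s epochs; analysis window 6 am to 10 pm; total-activity day of at least 10 h.

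**Step 1, threshold against window.** 45 < 60, so zeros confined to one lesson cannot meet the rule. The run must extend more than 60 − 45 = 15 min beyond the lesson before it is removed.

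**Step 2, the rule run on a synthetic day.** The monitor is worn from 7 am to 8 pm with non-zero counts throughout, except when removed around a lesson starting at 9 am. The rule was applied to the whole day and, separately, to data cut to the lesson first. The protocol does not state the order; whole-day is the natural reading.

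| Monitor off | Zero run | Whole-day data | Cut to lesson first |
|---|---|---|---|
| Lesson only | 45 min | kept as 0 | kept as 0 |
| Lesson + 5 min before + 5 after | 55 min | kept as 0 | kept as 0 |
| Lesson + 7 + 8 | 60 min | kept as 0 | kept as 0 |
| Lesson + 8 + 8 | 61 min | removed | kept as 0 |
| Lesson + 10 + 15 | 70 min | removed | kept as 0 |
| Uninterrupted 90-min double lesson | 90 min | removed | removed |

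In the first three rows the day is credited with 14.0 h: 13 h between 7 am and 8 pm, including the removal itself, plus the zero run from 6 to 7 am, which at exactly 60 min is also kept. The day passes 10 h, so a day-level check does not help.

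**Step 3, effect on one child.** With k lessons of equal true activity m and one false zero, the mean is (k − 1)m/k, a fall of 1/k.

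| k | 1 | 2 | 3 | 4 | 5 | 6 |
|---|---|---|---|---|---|---|
| Fall in lesson mean | 100% | 50% | 33.3% | 25% | 20% | 16.7% |

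Six lessons over five school days is 6/5 = 1.2 lessons per day, so a child admitted on one valid school day will often have k = 1. A child with a full school week has k of about 6.

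**Step 4, effect on the arms.** If a fraction p of counted lessons are false zeros, and equally so in both arms, each arm mean and their difference are multiplied by (1 − p). The document gives no value of p. As pure illustration, an assumed p of 2% to 10% would shrink the difference by 2% to 10%.

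**The case against.** The strongest reply is that this is a detail missing from a condensed article, and that the full protocol or analysis plan may hold a lesson-level wear rule. That possibility stands. But the article does not leave the matter open: it fixes the non-wear threshold and the inclusion criterion specific to lessons. Followed as written, those rules produce the false zero, so the point concerns a stated rule and not a silence.

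The second reply concerns weight, and most of it stands. Children were "instructed to wear the monitor during waking hours for at least eight consecutive days", and nothing in the document suggests that monitors came off for math. The 100% case needs a single counted lesson and a removal limited to it. Lesson activity is neither the primary outcome nor among the secondary outcomes listed in the *Abstract*, and teacher SMS reports and video give parallel information. A long zero-run threshold also has a purpose: it avoids classing real stillness as non-wear.

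A reader might infer more than the document supports in four places:

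- *Children who wore the monitor in lessons but for less than 10 h are lost from the lesson analysis.* The 10-h criterion is attached to total activity. Whether the one valid day for lessons inherits it is plausible but not stated.
- *The bias runs against the intervention because monitors come off more in active lessons.* Nothing in the document bears on removal by arm.
- *Accelerometry is the only device-based check on delivery.* Lessons were also filmed (*Video analysis*).
- *Lesson activity is the exposure in the secondary association analyses.* The *Background* names physical activity only in general.

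**Conclusion.** The concern holds in a narrow form and is minor. A removal around one lesson that leaves a zero run of 60 min or less is scored as a lesson without activity, and no other rule in the article catches it. The child's lesson mean falls by 1/k, from 100% with one counted lesson to about 17% with six. This assumes equally active lessons, one affected lesson, and processing as the article states. Longer removals are eliminated, provided that the rule runs on whole-day data. The size at arm level cannot be given, because the frequency of single-lesson removal is not reported. The consequence is confined to a compliance measure and to any association that uses it; the comparison of math scores does not depend on it.

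**What to change.** For math-lesson activity only:

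1. Treat a scheduled lesson whose counts are zero throughout as unworn and exclude it. At 10-s resolution that is 45 × 6 = 270 consecutive zero epochs, which is implausible for a worn monitor on a seven-year-old.
2. Average over the remaining lessons and require at least one worn lesson per child.
3. Report the result under the current rule as a sensitivity analysis, with the number of lessons excluded in each arm. That count also supplies the missing frequency.

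Keep the 60-min and 10-h rules for total activity.

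The cost is one further run on the stored 10-s data. The downside is that a rare, truly motionless lesson may be dropped; the sensitivity analysis shows whether that matters. A removal covering only part of a lesson would still pass. A shorter zero-run limit within the lesson would catch more of these but is not recommended: sitting periods are capped at 20 min in intervention lessons, while control lessons follow usual teaching, so such a limit could preferentially drop still control lessons and distort the contrast.

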### Statistics

Descriptive statistics according to outcome measures and relevant baseline characteristics will be calculated and compared across allocation groups.

Using conventional two-sided levels of significance (0.05) and statistical power (0.8) and given a sample size of 550 children from 12 different schools, the minimum detectable difference in the change in math score between the intervention and control group will be 0.9 points, assuming a standard deviation of the change in math score of 3.6 points. If a school-level cluster effect of 0.07 is taken into account, the minimum detectable difference in the change in math score will be 1.9 points.

The effect of the intervention will be tested using mixed effects regression models adjusted for relevant potential confounding factors that were not randomly distributed in children from the intervention and control schools (i.e. gender, age, baseline value of the variable, socioeconomic status). Because of the clustered nature of the data, schools will be included as random effects in the analyses. All data will be entered twice and thereafter checked manually for outliers. Analyses will be performed with statistical software STATA version 14.

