## Methods

### Study design

The study was designed as a cluster-randomized controlled trial with two arms. In two municipalities in the southern part of Denmark, twelve elementary schools were randomized to either active math intervention (*n* = 7) or control (*n* = 5) (Fig. 1). Randomization was performed by random selection of sealed envelopes containing the intervention allocation stratified by municipality, in the presence of school leaders, municipality representatives and study researchers.

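### The arm effect rests on 12 schools, and the article states nothing that holds the mixed-model test at 0.05; an uncorrected Wald z test would run at about 0.07 to 0.13

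*Protocol article*

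**What the plan says.** All references are to the protocol article.

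- Under Study design, "twelve elementary schools were randomized to either active math intervention" or control, with 7 schools in the intervention arm and 5 in the control arm, stratified by municipality.
- The Statistics section sets the operating characteristics: "Using conventional two-sided levels of significance (0.05) and statistical power (0.8"). The planning inputs follow: "given a sample size of 550 children from 12 different schools" and "assuming a standard deviation of the change in math score of 3.6 points".
- It gives two planning results. Without clustering, "the minimum detectable difference in the change in math score between the intervention and control group will be 0.9 points". With clustering, "If a school-level cluster effect of 0.07 is taken into account, the minimum detectable difference in the change in math score will be 1.9 points".
- On the analysis, "The effect of the intervention will be tested using mixed effects regression models". The examples of adjustment factors are gender, age, baseline value and socioeconomic status. School is a random effect and the software is Stata 14.

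The section does not mention ML or REML, a degrees-of-freedom method, a t reference, or a school-level or permutation test. It also does not mention a normal reference, and it does not rule out a correction.

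**The concern.** A whole school receives one arm, so the precision of the arm effect depends mainly on the between-school variance, which has to be estimated from 12 schools. Adding children within schools hardly changes this. Large-sample inference treats that variance as known and refers the estimate to the normal distribution. With 7 v 5 schools this is anti-conservative. ML makes it worse, because it also underestimates the between-school variance.

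The article fixes the level, the model, the random effect and the software, but not the element that decides whether the declared 0.05 is the true level. At stake are the false-positive rate for math achievement, the primary outcome, and confidence intervals that may be too narrow. The Discussion expects the results to serve schools and policy-makers as an evidence base. Leaving the reference open also leaves the choice between critical values of 1.96 and about 2.23 to 2.26 until after the data are seen.

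**Working it through.** **Inputs from the article.** Two-sided level 0.05; power 0.80; 550 children planned and 505 enrolled; 12 schools, 7 v 5; SD of change 3.6; ICC 0.07.

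**Assumed, not in the article.** School sizes, the arm split within municipality (taken as 4:3 and 3:2), normal outcomes, and ICC values other than 0.07.

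**Step 1: the plan's own figures.** MDD = (z.975 + z.80) × SD × √(1/n1 + 1/n2), multiplied by √DE for clustering.

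- No clustering, equal arms: 2.802 × 3.6 × √(4/550) = 0.86. With a 7:5 split it is 0.87. Both print as 0.9, as stated.
- Design effect: m = 550/12 = 45.83; DE = 1 + 44.83 × 0.07 = 4.14.
- Clustered, normal quantiles: 0.860 × √4.138 = 1.75 (equal arms) or 0.872 × √4.138 = 1.77 (7:5).
- Clustered, t quantiles on 10 df (2.228 + 0.879 = 3.107): 1.94 (equal arms), which prints as 1.9, or 1.97 (7:5), which prints as 2.0.
- Clustered, normal quantiles, 7:5, unequal schools, DE = 1 + ((1 + CV²)m − 1) × 0.07 with CV = 0.40: for 550 children DE = 4.65 and MDD = 0.872 × √4.65 = 1.88; for 505 children (m = 42.08) DE = 4.35 and MDD = 0.910 × √4.35 = 1.90.

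The printed 1.9 can therefore come from either distribution, depending on unstated inputs.

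**Step 2: degrees of freedom for arm.** 12 schools − 2 parameters (intercept, arm) = 10; with municipality, 9.

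**Step 3: analytic size of a z test.**

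- Unbiased variance, as an approximation to REML: 2 × P(t10 > 1.96) = 0.078; 2 × P(t9 > 1.96) = 0.082.
- Variance shrunk by df/12, as an approximation to ML: 2 × P(t10 > 1.96 × √(10/12)) = 0.104; 2 × P(t9 > 1.96 × √(9/12)) = 0.124.

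**Step 4: simulation with no arm effect.** Random school intercept, 7 v 5 schools, ICC 0.07, 4,000 runs per setting; Monte Carlo standard error near 0.08 is √(0.08 × 0.92/4000) = 0.004. School sizes were equal (about 46) or unequal (15 to 70). Three of the settings:

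| School sizes, model | ML, z | REML, z | REML, t (df) |
|---|---|---|---|
| Unequal, arm only | 0.102 | 0.081 | 0.050 (10) |
| Equal, arm + municipality | 0.119 | 0.084 | 0.050 (9) |
| Unequal, arm + municipality | 0.125 | 0.083 | 0.049 (9) |

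Across all settings at this ICC, REML with z gave 0.080 to 0.084 and ML with z gave 0.102 to 0.125. ML with t on 10 df gave 0.072 to 0.087, so a t reference alone does not repair an ML fit.

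A second set (505 children, 2,500 runs per setting) gave 0.073 to 0.080 for REML with z, and for ML with z 0.095 for arm only and 0.11 to 0.13 with municipality. A third gave about 0.07 to 0.09 (REML, z), 0.11 to 0.13 (ML, z) and 0.045 to 0.058 (REML, t on 9 or 10 df).

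**Step 5: dependence on the ICC.** In the 4,000-run set, a z test over ICC 0.03 to 0.20 gave 0.068 to 0.085 (REML) and 0.100 to 0.132 (ML). At ICC 0.01 it gave 0.059 to 0.085 over both estimators, and another set gave about 0.05 to 0.08. At ICC 0.01 with unequal schools, REML with t was conservative, at about 0.035 on 10 df (arm only) and on 9 df (with municipality).

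**The case against.** The strongest reply is that nothing wrong is stated. The article recognises school as the clustering unit, never says Wald z or ML, and a journal article commonly leaves the estimator and degrees-of-freedom method to a fuller document. This stands against any claim that the trial will be analysed without a correction or that its level is 0.07 to 0.13. It does not remove the conditional point. The article declares 0.05 and fixes the model, and under ordinary likelihood inference for that model with 12 schools the declared level is missed by a factor of about 1.6 (0.08/0.05) to 2.5 (0.125/0.05).

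Two stronger readings are tempting and should not be drawn.

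- A reader might infer that planning used a t distribution while the analysis uses a normal one. The article states no analysis distribution. As Step 1 shows, 1.9 also follows from a normal calculation with 7:5 arms and moderately unequal schools, while t on 10 df with 7:5 gives 1.97.
- A reader might infer that every secondary outcome is tested well above 5%. The only ICC in the article is the 0.07 used for change in math score, and at a low ICC the excess can be small.

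It is also fair to say that the top of the range needs ML, a z reference and a municipality term together, and municipality is not among the named adjustment factors. For arm only, the simulated figures are about 0.07 to 0.08 (REML) and 0.10 (ML).

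**Conclusion.** The point holds as a conditional one about the primary test. Twelve schools give the arm effect about 10 degrees of freedom, or 9 with municipality, and the article states nothing that protects its two-sided 0.05 level. With uncorrected Wald z inference at ICC 0.07, the size is about 0.07 to 0.09 under REML and about 0.10 to 0.13 under ML.

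The analytic values depend only on the number of schools and school-level parameters, and on between-school variation dominating the standard error. The simulated values also rest on the assumed school sizes, arm split and normal outcomes. Child-level covariates were not simulated, but they use almost no school-level degrees of freedom. For the secondary outcomes the direction is the same, but the size cannot be given without their ICCs.

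**What to change.** Add to the Statistics section: models are fitted by REML, and the arm effect and its 95% CI use Kenward-Roger or Satterthwaite degrees of freedom. A simpler alternative is a t reference on the number of schools minus the number of school-level parameters: 10 df, or 9 if municipality is in the model. These are different procedures, so name one. State the estimator and the degrees-of-freedom method together, since t with ML is not enough.

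Optionally, add a comparison of school means or a permutation test within municipality as a check. Under the assumed 4:3 and 3:2 split there are 35 × 10 = 350 allocations, enough for a test at 0.05.

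The cost is one sentence and a software setting. Compared with z-based intervals, the simple t intervals are about 14% wider on 10 df (2.228/1.960 = 1.137) and 15% wider on 9 df (2.262/1.960 = 1.154). For an outcome with a very low ICC the t test will be somewhat conservative.

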### Recruitment of participants

We approached three municipalities in the Region of Southern Denmark with the aim of recruiting schools and 1st grade children to the study. One municipality (15 schools) declined to participate. We hypothesized that children in this age group would particularly benefit from a classroom-based PA intervention, as they were likely to be struggling to sit in the same position in lessons for the majority of the day. Schools in these municipalities were eligible if they did not have a structured program that incorporated PA in the classroom.

Out of the 48 eligible schools that were invited to participate in the study, 12 schools accepted (7 in Svendborg municipality and 5 in Kolding municipality). The 1st grade children in these schools were invited to participate in a letter describing the study, measurement methods, randomization procedure and consent form. The children, parents and teachers were then invited to a meeting at the school, where a full description of the scientific background and the study was given. After this, 90.7 % of parents gave consent for their child to participate in the study, corresponding to 505 out of 557 students in 26 different classes. The excluded children received the same intervention as their classmates but did not participate in testing. A flowchart illustrating the recruitment and randomization process is shown in Fig. 1.

In Svendborg municipality, the participating schools were all part of an existing intervention study that had been initiated in 2008 (the CHAMPS-study DK). This intervention consisted of four extra lessons of physical education (PE) each week, in addition to the two compulsory lessons, resulting in a total of 4.5 h extra per week, divided over at least three weekly sessions of at least 60 min (a more detailed description of the CHAMPS-study DK can be found in [48]). To ensure that the extra PE lessons in Svendborg municipality did not bias the results of the present study, randomization to the intervention was stratified by municipality.

All schools were co-educational schools, with gender integrated classes in all subjects, which is typical for the Danish educational system.

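### Schools were randomised within municipality, but municipality is not in the stated model, so precision may be lost; it should be added, with school-level degrees of freedom

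*Protocol article*

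**What the plan says.** Under Study design, the 12 schools (7 intervention, 5 control) were allocated by "sealed envelopes containing the intervention allocation stratified by municipality". Recruitment of participants explains why. Seven schools came from Svendborg and five from Kolding, and every participating Svendborg school was already in a programme with four extra PE lessons a week. So that this would not distort the results, "randomization to the intervention was stratified by municipality".

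The Statistics section plans mixed effects regression with schools as random effects. Adjustment is for potential confounders that are not randomly distributed between the arms, listed as "i.e. gender, age, baseline value of the variable, socioeconomic status". Municipality is in neither part of the model, and no other section adds it.

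**The concern.** The plan treats the extra PE as able to influence the outcome and stratifies for that reason, then leaves the stratum out of the stated model. The covariate rule does not bring it back, because a factor balanced by stratification is not unevenly distributed between arms.

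Any mean difference between municipalities in math change then enters the school random effect. The design has largely removed that difference from the arm contrast, but the model still counts it as noise. With only 12 schools, between-school variance dominates precision. What is at stake is the gain that stratification was meant to bring: narrower intervals and more power for the primary comparison.

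**Working it through.** **1. The plan's own figures.** Inputs from Statistics: "given a sample size of 550 children from 12 different schools"; "assuming a standard deviation of the change in math score of 3.6 points"; ICC from "If a school-level cluster effect of 0.07 is taken into account"; two-sided 0.05; power 0.80.

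- No clustering, equal arms: 2.80 × 3.6 × √(2/275) = 0.86 (0.87 at 7:5). This agrees with "the minimum detectable difference in the change in math score between the intervention and control group will be 0.9 points".
- Design effect: 1 + (550/12 − 1) × 0.07 = 4.138.
- With clustering and normal quantiles: 0.86 × √4.138 = 1.75, which is not the stated 1.9.
- With t quantiles on 12 − 2 = 10 school-level df (2.228 + 0.879 = 3.107): 3.107 × 3.6 × √(2/275) × √4.138 = 1.94, which rounds to 1.9.

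The stated 1.9 is therefore reproduced when precision is judged on schools.

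**2. Variance of a school mean.** With the 505 enrolled children there are 505/12 = 42.1 per school, taken as equal.

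- Between schools: 0.07 × 3.6² = 0.907.
- Within schools: 0.93 × 3.6² / 42.1 = 0.286.
- Total 1.194, of which 76% is between schools.

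**3. Effect of the municipality term.** Two inputs are assumptions. The first is the split of arms within municipalities, taken as 4:3 and 3:2, since the text gives only 7:5 by arm and 7:5 by municipality. The second is the share f of between-school variance due to municipality, with total ICC held at 0.07. A share f corresponds to a municipality difference D = √(f × 0.907 / (7/12 × 5/12)).

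- MDD without municipality: 3.107 × √((1/7 + 1/5) × 1.194) = 1.99.
- MDD with municipality: 3.146 × √(0.3431 × ((1 − f) × 0.907 + 0.286)), where 3.146 is the multiplier on 9 df and 0.3431 is the design factor with municipality in the model.

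Size and power come from 200,000 simulated sets of 12 school means per scenario, with a t reference on 10 df (without) or 9 df (with).

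| f | D (points) | MDD without → with | Power at 1.9, without → with | True size without |
|---|---|---|---|---|
| 0 | 0 | 1.99 → 2.01 | 76% → 75% | 5.0% |
| 5% | 0.43 | 1.99 → 1.97 | 76% → 77% | 4.6% |
| 10% | 0.61 | 1.99 → 1.93 | 76% → 78.5% | 4.2% |
| 30% | 1.06 | 1.99 → 1.77 | 76% → 85% | 2.7% |

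With municipality in the model the size stays at about 5% throughout. At f = 30% the model without it reports a mean standard error of 0.64, while the estimate actually varies with SD 0.56. Break-even is at a share of about 3%.

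If the 1.06-point difference comes on top of an ICC of 0.07 rather than within it, power goes from 66% to 75%.

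**4. Bias.** Under the assumed split, the arms differ in the proportion of schools from Svendborg by 4/7 − 3/5 = −0.03. At D = 1.06 that shifts the estimate by about 0.03 points.

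**5. Reference distribution.** The article names none. If the statistic is compared with 1.96, the size at f = 30% is about 4.5% without municipality and about 8% with it. A t statistic on 9 df exceeds 1.96 in absolute value with probability 8.2%.

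**The case against.** - **The gain may be nil.** No section gives a municipality difference in math change. Stratification was a precaution, not evidence of a gap, and adjustment for baseline score and socioeconomic status may absorb part of any gap. At shares of 5% or less the gain is about one power point or none. This stands: only a range can be given.
- **The list may not be closed.** It describes child-level confounders, the article elsewhere uses the same abbreviation loosely before examples, and a fuller analysis plan might name the design factor. This weakens the point but does not remove it. The article states its adjustment set, the list reads naturally as complete, and its selection rule works against a balanced factor.
- **The split is assumed.** The flowchart is not available here. With 5:2 and 2:3, leaving municipality out would also shift the estimate, by (5/7 − 2/5) × 1.06 = 0.33 points at the 30% share. Including it removes that shift whatever the split.
- **The conservative direction presumes a t reference on school-level df.** This also stands, and the fix has to cover it.

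**Conclusion.** The stratification factor is missing from the stated model, and it should be added. If municipalities differ and the split within them is near-even, the standard error of the arm effect is too large and a t-test on school-level df is conservative. Under the assumptions above, the effect of adding municipality on power at 1.9 points runs from a loss of about 1 percentage point (no difference) to a gain of about 9 points (30% share).

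A reader might infer that the omission biases the trial or raises the false-positive rate. The article does not support that: with a near-even split the estimate barely moves, and the size falls below 5%. Nor can a definite power loss be claimed, since neither the municipality difference nor the split is given. This is a nearly free improvement that should be made, not a defect that invalidates the analysis.

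**What to change.** Add municipality as a fixed effect in the primary model and in every secondary between-arm model. State that the arm effect is tested with a small-sample degrees-of-freedom method, such as Kenward-Roger or Satterthwaite (about 9 school-level df), and not against a normal reference. The two changes belong together, because adding the term while keeping a normal reference would give a size of about 8%.

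Municipality is known for every school, so no new data are needed. The cost is one school-level degree of freedom (10 to 9), which raises the MDD from 1.99 to 2.01 points, about 1%, if the municipalities do not differ. A descriptive arm-by-municipality estimate is optional and not part of this fix.
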